## Abstract

**Background:**

In France, 62,000 hysterectomies are performed per year, 70% of which are benign. The choice of approach (laparotomy, laparoscopy or vaginal route) is particularly important in the case of large uterus (> 280g) which are associated with a higher risk of complications. The current data are not sufficient to favour one or other approach. A new medical device, the vNOTES (Natural Vaginal Orifice Transluminal Endoscopy System), offers the advantage of both laparoscopic and vaginal route for pelvic surgery.

**Objectives:**

To demonstrate the superiority in terms of intraoperative and postoperative complications of the use of a natural orifice transluminal endoscopic hysterectomy system (vNOTES) versus laparoscopic hysterectomy for benign pathologies on estimated large volume uteri (>280g)

**Materials and Methods:**

A randomised, double-blind, superiority trial will be performed at five hospital centres. Women with benign uterine pathology requiring hysterectomy and with a large uterus (> 280g) will be randomised to receive either laparoscopic or vNOTES hysterectomy.

**Main Outcome Measures:**

The primary outcome will be the occurrence of intraoperative and postoperative complications within 6 weeks of surgery. Secondary outcomes will be conversion during surgery, duration of surgery and hospitalisation, postoperative pain, postoperative complications, resumption of sexual life and satisfaction with the surgical team.

**Results:**

248 women will be randomised.

**Conclusion:**

This trial will provide a better understanding of the approach to large uteri optimise the care of these thousands of women undergoing hysterectomy.

**What's new?:**

This trial will evaluate the vNotes for large uteri.

## Introduction

In France, there are 62,000 hysterectomies performed per year, of which 70% are for benign indications (Lee et al., 2019).

The choice of surgical approach (laparotomy, laparoscopy or vaginal route) is particularly important in cases with large uteri (> 280g) as these are recognised to be associated with a high risk of complications and conversion. Currently minimally invasive approaches are recommended by the Collège national des gynécologues et obstétriciens français (CNGOF) (grade C) (Deffieux et al., 2015).

The vaginal and the laparoscopic route have their advantages and disadvantages.The latter is associated with an increased rate of conversion to laparotomy and post operative complications compared with vaginal hysterectomy (15% for the vaginal route, 37.5% for laparoscopy) and is particularly true for large uteri > 280g (Lee et al., 2019; Daraï et al., 2001; Gendy et al., 2011).

A Medical Device, the vNOTES (Natural Vaginal Orifice Transluminal Endoscopy System), offers the advantage of minimally invasive surgery by endoscopy through the vagina. Several feasibility studies in gynaecological surgeries have already been performed (Baekelandt, 2018a; Baekelandt, 2018b; Baekelandt et al., 2018c; Lowenstein et al., 2020; Baekelandt, 2019). Randomised trials have shown that the vNOTES allows hysterectomies to be performed without conversion with less pain, fewer postoperative complications and a shorter hospital stay when compared to laparoscopy (Baekelandt et al., 2019; Baekelandt et al., 2021). More recently, the developers of vNOTES found favorable results for vNOTES in terms of conversion and complication rates (Nulens et al., 2021) in large volume uteri (>280g).

The main objective of our study is to demonstrate the superiority in terms of intra and post operative complications within 6 weeks after surgery with the use of a vNOTES hysterectomy versus laparoscopic hysterectomy for benign pathologies on estimated large volume uteri (>280g).

## Material and Methods

### Type of study

This is a prospective, open-label, multicentre, randomised, parallel-group superiority study stratified on centre and uterine volume (280-500g; >500g). It evaluates conversion and intraoperative and postoperative complications within 6 weeks of surgery using the transluminal natural orifice vaginal endoscopic system for hysterectomies (vNOTES) versus laparoscopic hysterectomy.

### Population of study

The study will take place at the University Hospital of Saint-Etienne in the gynaecology- obstetrics department, at the Clermont Ferrand University Hospital and at the Issoire University Hospital, at the HCL HFME in Lyon and at the Clinique Mutualiste in Saint-Etienne.

This study is intended for any woman who is seen in a preoperative consultation in the Gynaecology-Obstetrics department of an investigating centere for a benign pathology of a large uterus requiring a hysterectomy.

The inclusion criteria will be: patients over 18 years old, affiliated or entitled to a social security system, having given their agreement to participate and after signing the consent form, presenting with a benign pathology of the uterus requiring a hysterectomy and having a large uterus estimated at more than 280g. A uterus will be defined as large if it corresponds to a gravid uterus of 12 weeks size, the 2D ultrasound or MRI measurements estimate the volume >280g with the formula LxWxAP, or by measurement of a volume in 3D ultrasound with the software VOCAL.

The exclusion criteria will be non-French- speaking patients, those who have not given their consent to participate in the study,are subject to a legal protection measure, unable to express their consent or those with a contraindication to the use of vNotes (endometriosis).

This study is currently being reviewed by the ethics committee.

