### Sample size calculation

Based on the figures found in two studies on large uteri (Daraï et al., 2001; Hwang et al., 2002) and Baekelandt’s study of hysterectomies (Baekelandt et al., 2019), for an alpha risk of 5% and a power of 90%, a superiority study with an expected complication rate of 37% with laparoscopy and 15% with the vaginal route (i.e. an RR of 0.5 and therefore a relative reduction in risk of 50%) will need to include 119 patients per group, i.e. 236 in total. In order to compensate for possible loss of sight, 248 patients will be included.

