### Study design

An information brochure on the study will be given to all patients who meet the inclusion criteria of the study at the preoperative consultation. An evaluation of pain by EVA scale will be carried out during this consultation.

After obtaining the patient’s consent on the day of the operation, the allocation between the two groups will be done by randomisation. This randomisation will be stratified on the centre and uterine volume (280-500g; > 500g). The randomisation list will be a randomised computer list established before the beginning of the study. It will be balanced by blocks of variable size and centralised via the Ennov Clinical web platform.

Two groups of patients will be constituted: a “laparoscopic approach” group and a “vNOTES” group. Patients will not know their group of assignment.

All hysterectomies will be performed by vNOTES-trained surgeons (20 procedures performed) who will follow the standard operating procedure. In women assigned to the experimental arm, the surgeon will perform a hysterectomy with the vNOTES medical device. In the women assigned to the control arm, the surgeon will perform a laparoscopic hysterectomy.

A questionnaire assessing visual comfort, feeling of safety and satisfaction on Lickert scales will be completed immediately after surgery by the operator and the operating assistant.

The care provided by the anesthetists and nurses will be standardised and similar in both groups. To limit bias, in all cases the patient will have abdominal dressings as if it underwent a laparoscopy.

Once returned to the ward, all participants will be assessed every 2 hours and discharged home when the patient’s condition allows(Chung score ≥ 9/10).

Telephone interviews by the department CRA, blinded to the allocation group will be conducted daily for the first week to assess postoperative pain.

A follow-up visit by an independent adjudication committee, blinded to the allocated group will be performed 6 weeks postoperatively or earlier if a complication brings a patient to consult.

Finally, a telephone call will be made at 3 months to evaluate the sexual impact by a questionnaire (PISQ12 with a score ranging from 0 to 48) (Table I).

**Table I t001:** Conduct of the study.

Visits	V1	V2	V3	V4	V5	V6
Title of the visit	Pre-operative selection visit	Day of the intervention	Immediate post-operative follow-up	Telephone follow-up D1-D7	Post-operative visit at 6 weeks	Questionnaire at 3 months
Information	X					

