### Data collection

Demographic data including age, weight (kilograms), height (cm), BMI (Kg/m2), medical, surgical and obstetric history will be collected directly in the observation notebooks as the study visits take place.

Also collected will be the uterine volume, estimated by pelvic ultrasound or by pelvic MRI if available, the benign uterine pathology requiring the intervention (fibroid, adenomyosis, endometrial hyperplasia, bleeding), the general condition of the patient, the solidity of the vaginal suture, postoperative pain and use of analgesics, the possible occurrence of the above-mentioned complications and sexual disorders with the PISQ 12 scale. These data will be validated by the investigator who will sign the observation notebooks. Missing data will be justified.

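### The printed 2D ultrasound/MRI size formula, L x W x AP, omits the ellipsoid factor, so a uterus of about 147 mL can pass the 280 g entry limit

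*Protocol article*

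**What the plan says.** Under Population of study, the protocol article requires "having a large uterus estimated at more than 280g" and then gives three alternative ways to establish it:

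- Clinical size: "A uterus will be defined as large if it corresponds to a gravid uterus of 12 weeks size".
- 2D ultrasound or MRI: "the 2D ultrasound or MRI measurements estimate the volume >280g with the formula LxWxAP".
- 3D ultrasound: "or by measurement of a volume in 3D ultrasound with the software VOCAL".

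The product of the three diameters is the only formula printed. The article gives no multiplying constant and no conversion from volume to grams.

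Randomisation uses size as well. Type of study describes the trial as "stratified on centre and uterine volume (280-500g; >500g"), and Study design repeats this. Neither section says how the volume for the stratum is obtained. Data collection adds: "Also collected will be the uterine volume, estimated by pelvic ultrasound or by pelvic MRI if available".

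**The concern.** Length x width x antero-posterior diameter is the volume of a box around the uterus. A rounded organ fills only part of that box, so the product always overstates its volume. The VOCAL volume has no such inflation. One sentence therefore puts the same uterus on two scales that differ by almost a factor of two. Because the routes are alternatives, the looser one sets the effective limit for any woman sized by 2D ultrasound or MRI.

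The 280 g limit defines the trial's objective and its population. It also carries the Introduction's rationale that large uteri have a high risk of complications and conversion. If clearly smaller uteri can enter, the result may not apply to the population named. On the article's own premise, the complication rate on which the sample size rests could also be lower than planned.

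**Working it through.** The 280 g limit is a chosen cut-off, so there is no plan figure to reproduce. The check is what the printed formula implies at that cut-off.

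**Inputs**

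- Entry limit 280 g, and formula L x W x AP for 2D ultrasound and MRI (Population of study).
- Strata 280-500 g and above 500 g (Type of study; Study design).
- Ellipsoid factor pi/6 = 0.5236. This is geometry, not in the article, and assumes a roughly ellipsoidal uterus. Assumed range for other shapes: 0.5 to 0.6.
- Density: assumed 1.0 g/mL, range 0.95 to 1.05. Not in the article.

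**Step 1: overstatement.** Box / ellipsoid = 1 / 0.5236 = 1.91. For shape factors 0.6 and 0.5: 1 / 0.6 = 1.67 and 1 / 0.5 = 2.0.

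**Step 2: what a product of 280 means.** Diameters are in cm, so the product is in mL.

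- Ellipsoid: 280 x 0.5236 = 147 mL.
- Shape range: 280 x 0.5 = 140 mL; 280 x 0.6 = 168 mL.
- In grams, with pi/6: 147 x 0.95 = 139 g; 147 x 1.05 = 154 g.
- Most favourable corner of both ranges: 280 x 0.6 x 1.05 = 176 g, still far below 280 g.

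Example: 9 x 6 x 5.2 cm gives a product of 281 and passes, but the ellipsoid volume is 281 x 0.5236 = 147 mL.

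**Step 3: the product that a true 280 needs.** 280 / 0.5236 = 535. With density 0.95 to 1.05, a true 280 g needs 563 to 509. Example: 10 x 8 x 6.7 cm gives a product of 536 and an ellipsoid volume of 281 mL.

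**Step 4: strata, only if they use the same product.**

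- A true 280 mL uterus has a product of about 535 and would be placed in the stratum above 500 g. This holds for any shape factor below 280 / 500 = 0.56. At 0.6 the product is 280 / 0.6 = 467, and the uterus stays in the lower stratum.
- A product of 500 is 500 x 0.5236 = 262 mL (250 mL at 0.5, 300 mL at 0.6).

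**Step 5: illustration of the effect on power.** The article does not give complication rates by uterine size, so the control rates below are assumed. Inputs are 119 per group, a relative risk of 0.5, two-sided 5%, and the normal approximation:

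Power = Phi{[(p1 - p2) - 1.96 x sqrt(2 x pbar x (1 - pbar) / 119)] / sqrt([p1(1 - p1) + p2(1 - p2)] / 119)}, with pbar the mean of p1 and p2.

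| Control rate p1 | p2 | Power |
|---|---|---|
| 37% (planned) | 18.5% | about 90% |
| 30% (assumed) | 15% | (0.150 - 0.106) / 0.0533 = 0.82, about 80% |
| 25% (assumed) | 12.5% | (0.125 - 0.099) / 0.0499 = 0.52, about 70% |

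The relative risk of 0.5 is used because it gives roughly the stated 119 per group. The table shows only how sensitive power is to the control rate. It does not predict that rate.

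**The case against.** The best defence is that this is a condensed article. The governing criterion is the 280 g limit, the formula is mentioned only briefly, and the full protocol or case report form may carry the constant. That is plausible, and it limits what can be said about how the trial will be run. It does not rescue the printed rule. The article states an operational entry formula, not a detail left to another document, and as stated the formula conflicts with its own limit.

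A second defence is that sizing takes place before allocation. This stands. Eligibility is checked at the preoperative visit and randomisation follows on the day of surgery, so any overestimate applies to both arms and does not bias the comparison. The article's primary analysis, a relative risk with Fisher's exact test, names no stratum adjustment, so misplaced strata would mainly weaken the balance on size.

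The objection is also right against several stronger readings that a reader might infer:

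- *The strata are wrong by the same factor.* The article gives no formula for them. Use of the product is plausible, because Data collection takes the volume from ultrasound or MRI, but it is not stated.
- *The whole 280-500 g stratum lies below the entry limit.* With pi/6 it would, but at a shape factor of 0.6 the upper edge is 300 mL.
- *A woman who qualifies on 12-week size has no volume and cannot be stratified.* She needs none to qualify, but Data collection plans an imaging volume without excepting her.
- *Many women with ordinary-size, low-risk uteri will be enrolled.* The article gives no size distribution, no share of women by route and no complication rate by size.

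**Conclusion.** The point holds for the 2D ultrasound/MRI eligibility route. As printed, the formula overstates uterine volume about 1.9-fold (1.67 to 2.0), and a uterus of about 147 mL (140 to 168 mL) can be admitted as larger than 280 g. That is inconsistent with the VOCAL route and with the stated population. The figures rest on an approximately ellipsoidal shape and a density near 1 g/mL, but no value in the assumed ranges closes the gap.

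About half describes the smallest uterus that this one route can admit, not the typical enrolled uterus. The 12-week and VOCAL routes are unaffected by the formula. The consequence for the strata is conditional on their using the same product.

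The harm is to applicability and possibly to the event rate. The direction of the latter follows from the article's premise that large uteri carry higher risk, but its size cannot be determined from the article. There is no bias between arms.

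**What to change.** Reconcile the article with the full protocol. In the eligibility definition, replace the product with L x W x AP x 0.52 (pi/6) for 2D ultrasound and MRI, and state the mL-to-g conversion. Assign the randomisation stratum from the imaging volume that is already to be collected, expressed on this common scale whether it comes from 2D ultrasound, MRI or VOCAL, and say so in Study design.

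This does not require removing clinical 12-week size as a route to eligibility. Whether it may stand alone is a separate design preference.

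The cost is a one-line change to the eligibility text and to the randomisation form. Some women who qualify by the box product would no longer do so, so recruitment may be slower. The change should precede enrolment, because eligibility and stratum cannot be reassigned after randomisation.

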### Sample size calculation

Based on the figures found in two studies on large uteri (Daraï et al., 2001; Hwang et al., 2002) and Baekelandt’s study of hysterectomies (Baekelandt et al., 2019), for an alpha risk of 5% and a power of 90%, a superiority study with an expected complication rate of 37% with laparoscopy and 15% with the vaginal route (i.e. an RR of 0.5 and therefore a relative reduction in risk of 50%) will need to include 119 patients per group, i.e. 236 in total. In order to compensate for possible loss of sight, 248 patients will be included.

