### Statistical analysis

The included population will described globally and by group (vNOTES vs laparoscopic approach). The main analysis will be performed according to the intention-to-treat principle. The frequency of patients presenting with at least one complication will be estimated in each group, as well as the 95% confidence interval of this frequency. The effect of the surgical strategy will be estimated by the relative risk and the 95% confidence interval. The resulting p-value of Fisher’s exact test will also be given. As the secondary objectives are exploratory, no statistical test will be performed (i.e. no p-value will be estimated), according to the new NEJM recommendations.

For the qualitative secondary endpoints, the relative risk and its confidence interval will be given. For quantitative endpoints, differences in means will be calculated, as well as their 95% confidence intervals.

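### The sample-size paragraph contradicts itself: 37% vs 15% is an RR of 0.41, not 0.5; those rates do not lead to 119 per group; and 119 per group is not 236

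*Protocol article*

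**What the plan says.** All the planning figures stand in one paragraph of the Protocol article, Sample size calculation. The error rates are given as "for an alpha risk of 5% and a power of 90" per cent, without saying whether alpha is one- or two-sided. The effect is "an expected complication rate of 37% with laparoscopy and 15% with the vaginal route", which the same sentence restates as "i.e. an RR of 0.5 and therefore a relative reduction in risk of 50" per cent. From this the trial "will need to include 119 patients per group, i.e. 236 in total". The allowance for losses follows: "In order to compensate for possible loss of sight, 248 patients will be included". No loss rate and no sample-size formula are given.

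Two other places bear on it. The Introduction gives slightly different rates, "15% for the vaginal route, 37.5% for laparoscopy". The Statistical analysis section estimates the effect by the relative risk with its 95% confidence interval and adds: "The resulting p-value of Fisher’s exact test will also be given". No other test is named for the primary outcome.

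**The concern.** The paragraph gives two effects as if they were one. A fall from 37% to 15% is 22 percentage points; a halving of 37% is 18.5 points, to 18.5%. These need clearly different sample sizes, and the printed arm size suits the second while the printed rates state the first. The arm size and the total also disagree.

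This paragraph is the only justification for randomising 248 women to one of two operations. As written, a reader cannot tell which reduction the trial is designed to detect, and so cannot judge a null result against a defined design effect. Nor can an ethics committee tell whether 248 is more than the stated effect requires, or about right for a smaller one.

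**Working it through.** **Inputs.** From Sample size calculation: alpha 5%, power 90%, rates 37% and 15%, RR 0.5, 119 per group, total 236, 248 randomised. From the Introduction: 37.5% and 15%. From Statistical analysis: Fisher's exact test. Assumed: two-sided alpha and 1:1 allocation, so z = 1.960 and 1.282, and (1.960 + 1.282)² = 10.507.

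**Step 1: the RR.** 0.15/0.37 = 0.405, a reduction of 59%. With the Introduction's control rate, 0.15/0.375 = 0.40. Rounding does not turn either into 0.5. An RR of 0.5 means 18.5% against 37%, or 18.75% against 37.5%.

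**Step 2: trying to reproduce 119 from the printed rates.**

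- Unpooled: n = 10.507 × [p1(1−p1) + p2(1−p2)]/(p1−p2)² = 10.507 × (0.2331 + 0.1275)/0.22² = 78.3, so 79 per group.
- Pooled: n = [1.960 × √(2p̄(1−p̄)) + 1.282 × √(p1(1−p1) + p2(1−p2))]²/(p1−p2)², with p̄ = 0.26, gives 81.4, so 82 per group.
- With continuity correction: 90.3, so 91. By exact Fisher power: 89.
- One-sided alpha lowers the need further, to 64 to 76 per group depending on the method.

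No variant at the stated inputs gives 119.

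**Step 3: the same formulas at RR 0.5** (two-sided 5%, 90% power).

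| Rates | Unpooled | Pooled | Fisher |
|---|---|---|---|
| 37% vs 15% | 78.3 → 79 | 81.4 → 82 | 89 |
| 37% vs 18.5% | 117.9 → 118 | 121.0 → 122 | 131 |
| 37.5% vs 18.75% | 115.6 → 116 | 118.7 → 119 | 129 |

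The printed size lies in the RR 0.5 rows, by normal approximation without continuity correction. Two routes fit about equally well: 37% vs 18.5% unpooled gives 118 per group, and 2 × 118 = 236, the printed total; 37.5% vs 18.75% pooled gives 119, the printed arm size. Keeping 15% and RR 0.5 together would imply a control rate of 30%, which needs 158 (unpooled) or 161 (pooled) per group; that fits neither the printed size nor either control rate in the document.

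**Step 4: totals and losses.** 2 × 119 = 238; 236 = 2 × 118. The margin up to 248 is 12/248 = 4.8% from 236, or 10/248 = 4.0% from 238.

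**Step 5: power under Fisher's exact test**, two-sided, by full enumeration of both binomial distributions.

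| Rates | 118 per group | 119 per group | 124 per group (all 248 evaluable) |
|---|---|---|---|
| 37% vs 15% | 96.7% | 96.8% | 97.3% |
| 37% vs 18.5% | 86.8% | 87.1% | 88.4% |
| 37.5% vs 18.75% | 87.5% | 87.7% | 89.0% |

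For comparison, the uncorrected normal-approximation test at 119 per group has 89.5% and 90.1% power in the two RR 0.5 rows.

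**The case against.** The best case for leaving the design alone is that little follows for the trial itself. Under any of these readings 248 women give roughly 87 to 97% power. The 236 against 238 is a two-patient slip. The Fisher shortfall is 2 to 3 points at 119 per group, 1 to 2 points if nobody is lost, and arises only if RR 0.5 is the planning effect. The relative risk with its interval is the first-named analysis, with the Fisher p-value beside it, and sizing by a normal approximation before testing with Fisher's test is a common and small mismatch. All of that stands, and it is why the remedy is a correction of wording and not a larger trial.

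It does not remove the contradiction. The figures are printed and disagree, so neither condensation into an article nor an analysis plan that is not shown can explain them. No choice of sidedness reconciles 37% vs 15% with an RR of 0.5 or with 119.

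Some stronger readings are tempting but not supported:

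- A reader might infer that 119 can only have come from 37.5% vs 18.75%, so that 238 is the true total and 236 the error. The unpooled result for 37% vs 18.5% yields 236 exactly, so 119 may equally be the slip.
- A reader might infer that the loss allowance was inflated by multiplying by 1.05 where division by 0.95 was needed. No loss rate is stated, and 236 × 1.05 = 247.8 and 236/0.95 = 248.4 both round to 248.

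**Conclusion.** The paragraph is wrong as written. The rates, the RR, the arm size and the total do not belong together: RR 0.41 against a stated 0.5; about 79 to 82 per group (about 90 with Fisher's test or a continuity correction) against a stated 119; and 238 against a stated 236. The printed size fits an RR of 0.5, but the document does not show which pair of rates or which formula produced it. Under Fisher's test with 119 per group, the stated 90% is too low at the printed rates (about 97%) and slightly too high at RR 0.5 (about 87 to 88%, or 88 to 89% if all 248 are evaluable).

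The mismatch between 0.41 and 0.5, and between the totals, is plain arithmetic and needs no assumption. The sample sizes and powers assume two-sided 5% alpha and equal groups. A reader might conclude that the trial is seriously underpowered; the figures do not support that. What is missing is a single, identifiable effect to which the 90% refers.

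**What to change.** Keep 248 and rewrite the paragraph so that it states:

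- the one pair of rates actually used for planning, with the RR that follows from it;
- a per-group number and a total that agree;
- the loss allowance as a rate, and whether alpha is one- or two-sided;
- the power for that effect under Fisher's exact test: about 97% with RR 0.41 if 15% is the real expectation, or about 87 to 88% at 119 per group if RR 0.5 is the target.

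The sponsor must supply the planning effect from its own records; it should not be chosen now to match the sample size. The cost is one paragraph and no extra patients. The downside is a slightly less favourable stated power if RR 0.5 is the target.
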